# The efficacy and safety of the herbal medicine *geonchildan* for patients with active rheumatoid arthritis: study protocol for a randomized, double-blind, placebo-controlled, parallel pilot trial

**DOI:** 10.1186/s13063-018-2849-3

**Published:** 2018-09-03

**Keywords:** Geonchildan, Rheumatoid arthritis, Herbal medicine, Randomized clinical trial, Study protocol

## Abstract

**Background:**

This study aims to assess the efficacy and safety of *geonchildan*, a Korean traditional herbal medicine, for patients with active rheumatoid arthritis (RA) and evaluate the feasibility of a large-scale confirmatory clinical trial.

**Methods/design:**

This is a randomized, double-blind, placebo-controlled, parallel two-arm pilot trial in Seoul, Korea. Altogether, 30 patients diagnosed with RA for at least 3 months and with a Disease Activity Score for 28 joints (DAS28) ≥ 3.2 will be enrolled. Participants are randomly assigned to one of two groups, the experimental group or the placebo group, in a 1:1 ratio and will make four scheduled visits. The participants will be administered *geonchildan* or a placebo three times per day for 12 weeks. The change in DAS28 will be examined as the primary efficacy outcome. The secondary efficacy outcomes include the proportion of patients achieving ACR20, ACR50, ACR70, and EULAR responses; the DAS28 sub-items; the consumption of medication; Korean Health Assessment Questionnaire scores; inflammatory parameters; and the Korean medical diagnostic pattern indicator. Adverse events and laboratory test results will be recorded to evaluate safety. The process, resources used, and management of the study will also be assessed to determine the feasibility of a large-scale trial.

**Discussion:**

This is the first clinical trial to explore the efficacy and safety of *geonchildan* in patients with active RA. If the superiority of *geonchildan* versus the placebo is demonstrated and the study design is feasible, this study could form the foundation for a large-scale clinical trial. The results will be published in a peer-reviewed journal.

**Trial registration:**

Clinical Research Information Service, KCT0001943. Registered on 14 June 2016.

**Electronic supplementary material:**

The online version of this article (10.1186/s13063-018-2849-3) contains supplementary material, which is available to authorized users.

## Background

Rheumatoid arthritis (RA) is the most common autoimmune inflammatory disease. It affects 0.5 to 1.0% of the population worldwide, causing chronically progressive inflammation [1]. It is characterized by severe joint damage, loss of physical function, distress, and poor quality of life. Whilst the early use of disease-modifying antirheumatic drugs (DMARDs), such as methotrexate, is recommended to achieve complete or long-lasting remission, a substantial number of patients experience lasting disease activity and require additional DMARDs or biological drugs [2]. These drugs are known to induce a considerable number of adverse events (AEs), even life threatening ones, which has led an increasing number of patients with RA to seek complementary and integrative medicine, including herbal medicines [3].

Several randomized controlled trials (RCTs) have been conducted to identify the efficacy and safety of herbal medicines for treating RA, but confirmatory conclusions have not been drawn due to methodological flaws and inadequate reporting [1]. Extracts of *Tripterygium wilfordii*, commonly known as thunder god vine, are among the most well-known herbal medicines used for RA in China and researched in China. Several studies have shown that these may reduce some RA symptoms compared to a placebo [4–7]. However, the usefulness is controversial because the oral use of these extracts may be associated with several side effects [1].

*Geonchildan* is a herbal decoction of *Rhus verniciflua* Stokes. This plant in the *Anacardiaceae* family has long been used as an ingredient in arthritis medication in East Asian traditional medicine [8]. Some experimental studies have reported that *Rhus verniciflua* Stokes has marked antioxidant and anti-inflammatory effects, supporting its use for RA [9–11]. In particular, a recent study showed that the flavonol-rich *Rhus verniciflua* Stokes and its major compound, fisetin, suppress some inflammatory cytokines and chemokines and also angiogenic factors in IL-1β-stimulated RA fibroblast-like synovial cells and inflammation-related mouse models [11].

In Kyung Hee University Korean Medicine Hospital, *geonchildan* has been prescribed to patients with RA since 2011. However, no prospective clinical trials have yet evaluated the effects of *geonchildan* for patients with RA. Therefore, we have designed a randomized, placebo-controlled, double-blind, exploratory pilot clinical trial to assess the efficacy and safety of *geonchildan* in the treatment of patients with RA and to evaluate the feasibility of a large-scale confirmatory clinical trial.

## Methods/design

### Objectives

The primary aim of this study is to determine if *geonchildan* is superior to placebo at decreasing the Disease Activity Score for 28 joints (DAS28) from baseline after 12 weeks of treatment. The secondary outcomes of this study are as follows:proportion of patients achieving ACR20, ACR50, ACR70, and European League Against Rheumatism (EULAR) responsesDAS28 sub-itemsconsumption of medicationKorean Health Assessment Questionnaire (KHAQ) scoresinflammatory parametersKorean medical diagnostic pattern indicator (12-item Blood Stasis Questionnaire or BSQ)

We hypothesize that these outcomes will improve more significantly in the group receiving *geonchildan* than in the group receiving the placebo after 12 weeks of treatment and that *geonchildan* is a safe treatment as verified using blood tests, vital signs, chest radiography, and electrocardiography (ECG). This study design will be assessed to see if the process, resources used, and management are feasible for a large-scale confirmatory trial.

### Design and setting

This study is a randomized, double-blind, placebo-controlled, parallel, pilot clinical trial. After voluntarily signing informed consent, participants who are eligible for this study are assigned randomly to one of two groups (the experimental group or the placebo group) with a 1:1 allocation ratio. Patients will be administered one capsule of *geonchildan* or placebo three times per day for 12 weeks.

#### Recruitment strategy

The participants will be recruited from the Acupuncture and Moxibustion Department of Kyung Hee University Korean Medicine Hospital in Seoul, Korea. A total of 30 patients with RA will be recruited through publicity such as broadcast media, newspapers, the hospital’s homepage, and advertisements in nearby welfare centers and subway stations. Screening will continue until 30 participants have been enrolled. The estimated recruitment period is from January 2017 to July 2018.

#### Study plan

After participants have consented voluntarily to the study at the first visit, they will be screened using the survey measures, blood and urine tests, chest radiography, and ECG. The results of the tests will be conveyed by telephone to them and patients who meet the inclusion criteria will be requested to visit for randomization within 2 weeks of the screening visit. Patients who use nonsteroidal anti-inflammatory drugs (NSAIDs) for other diseases will be eligible to participate in the study after a 2-week washout period. On the second visit, patients will be randomly assigned to one of the two groups and will be provided with the investigational drugs. Participants will be administered one capsule of *geonchildan* or placebo three times per day for 12 weeks. During the 12 weeks of treatment, participants will be free to continue with their standard treatment with methotrexate, NSAIDs, or steroids, without modification. Moreover, one additional visit will be scheduled 6 weeks after randomization. A total of three visits will take place during the treatment period. A flow chart of the study process is shown in Fig. 1. This trial protocol was developed according to the Standardized Protocol Items: Recommendations for Interventional Trials (SPIRIT) guidelines (see Additional file 1) [12].

**Fig. 1 Fig1:**
[figure not shown]
A flow chart of the study process

### Types of participants

#### Inclusion criteria

Participants who meet the following conditions will be included:Men and women aged 19 to 75 yearsPatients who have been diagnosed with RA according to the 2010 ACR/EULAR classification criteria and have had RA for at least 3 months prior to enrolmentPatients with active RA (DAS28 ≥ 3.2)Patients who have taken methotrexate for more than 3 months; the dose of methotrexate should have been maintained for at least 8 weeks before participation in the trial (7.5–20 mg/week oral or equivalent injection dose)Patients with at least three swollen joints and three tender joints

To participate, patients must provide informed consent in writing after being informed of the purpose and characteristics of the study.

#### Exclusion criteria

Participants will be excluded if any of the following conditions are satisfied:Patients with at least one of the following laboratory abnormalities at screeningWhite blood cell count ≤3000/mm^3^Hemoglobin < 8.5 g/dLPlatelet count < 100,000/mm^3^Serum creatinine > 2.0 mg/dLAspartate transaminase or alanine transaminase at least twice the upper limit of the normal rangePatients who have had or have planned a surgical procedure for RA.Patients with severe infections including major respiratory diseases or who have received systematic antibiotics within 2 weeksPatients with clinically uncontrolled cardiovascular diseasePatients with a history of malignancy within 5 years (however, patients who have a history of completely treated nonmelanoma skin cancer or uterine cervical cancer may be included)Patients with autoimmune diseases other than RAPatients with a history of severe hypersensitivity or allergic reaction to the investigative drug or *Rhus verniciflua* Stokes (e.g., poison ivy dermatitis)Patients who have participated in other clinical studies within 3 months of screeningPatients with medical or psychological contraindications for the investigative drugPatients who are pregnant, plan to become pregnant, or will be breast-feeding during the clinical trialPatients with difficulty moving voluntarily, with high disease activity, or who are unsuitable for study inclusion in the investigator’s judgmentPatients who have received a steroid injection into the glenoid cavity of the evaluation joint within 4 weeks of screeningPatients who have received oral steroids of more 10 mg per day, have newly started treatment within 4 weeks of screening, or have changed their dose of steroids within 2 weeks of screeningPatients who have newly started treatment with NSAIDs within 4 weeks of screening or have changed their dose of NSAIDs within 2 weeks of screening.Patients who have received biological medicine or cell proliferation inhibitors before screeningPatients who have received DMARDs except methotrexate before screeningPatients who are being treated for liver or kidney disease

### Blinding

The participants, outcome assessors, study monitors, data managers, and statisticians will be blinded to the allocation. If possible, participants will be advised not to compare their investigational drugs with each other. The allocation guessing for blinding test will be conducted at the last visit by participants. They will choose one of the following three options based on their personal feeling about the drug they received: 'real drug', 'placebo drug', or 'do not know. The blinding will be maintained until all 30 participants have completed the study, the data analysis is complete, and the database is locked.

Separate emergency codes will be opened only if the researchers must inform a participant of which investigational drugs they are receiving (e.g., to determine the subsequent treatment to manage a serious AE).

### Intervention

The total dose of each capsule of *geonchildan* is 447 mg, of which 200 mg is a dried herbal extract. The herbal extract was obtained from the cortex of *Rhus verniciflua* Stokes. The plant material and the sample were deposited in the herbarium of the Quality Control Department of Hanpoong Pharm and Foods Co., Ltd. (Wanju-Gun, South Korea). The raw materials were extracted with water at 90–100 °C for 2 h and filtered. The process was repeated four times. The filtrate was vacuum-dried to yield *geonchildan* extract (yield, 5.0%). A high-performance liquid chromatography analysis was performed to quantify the chemical constituents of the herbal extract. The herbal extract of *geonchildan* was controlled so that it contains more than 4.99 mg/g of fisetin (C_15_H_10_O_6_) and less than 5 ppm of urushiol. To test the purity, heavy metal tests, residual pesticide tests, and a microbial limit test were conducted according to the Korea Pharmacopeia. The items tested for included total heavy metals, lead (Pb), arsenic (As), dichlorodiphenyltrichloroethane, benzene hexachloride, aldrin, dieldrin, endrin, total number of aerobic microorganisms, total number of fungi, *Escherichia coli*, *Salmonella*, *Pseudomonas aeruginosa*, and *Staphylococcus aureus*.

The placebo capsules that will be used in the trial are filled with a powder that resembles the herbal extract. The powder is made of lactose hydrate, colored with caramel, and flavored with a ginseng-like fragrance. The *geonchildan* and placebo capsules are manufactured so that there is no difference in shape, color, size, odor, or taste. All manufacturing processes for the *geonchildan* and placebo capsules were conducted at Hanpoong Pharm and Foods Co., Ltd., according to the Korean Good Manufacturing Practices.

Participants will ingest one capsule of *geonchildan* or placebo, three times per day for 12 weeks. This dosage regimen was determined after a clinical chart review (data not shown). During the 12 weeks of treatment, participants will comply with the study protocol by visiting the clinic every 6 weeks and undergoing a scheduled examination. If AEs due to the investigational drugs occur, the researchers will alter the dose or frequency according to internal guidelines.

#### Permitted concomitant treatments

Methotrexate administered for more than 3 months with the dose maintained for at least 8 weeks will be allowed without a dose change during the study period. Oral steroids (less than 10 mg per day) and NSAIDs started for at least 4 weeks with the dose maintained for at least 2 weeks will be permitted and any change of dose will be recorded. Other drugs that are unrelated to RA will be permitted if they have been administered for more than 30 days before the screening visit. Participants who use NSAIDs and do not satisfy the above-mentioned criteria can participate after a 2-week washout period.

#### Prohibited concomitant treatments

Prohibited drugs include agents that can affect RA and the primary outcome, such as (1) DMARDs except methotrexate, (2) steroid injections, (3) oral steroids at a dose higher than 10 mg per day or administered for other diseases, (4) NSAIDs administered for other diseases, and (5) biological medicines, cell proliferation inhibitors, or immunosuppressants.

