#### Primary outcome measurement

Changes in DAS28 based on erythrocyte sedimentation rate (ESR) scores will be used as the primary outcome measurement. The DAS28 is a validated and widely accepted measure for RA disease activity and consists of four components: number of tender joints out of 28, number of swollen joints out of 28, C-reactive protein or ESR, and the patient’s global assessment of disease activity on a visual analogue scale (VAS) (0–100 mm). Scores of 2.6 to ≤3.2, <3.2 to ≤5.1, and >5.1 represent low, moderate, and high disease activity, respectively [13, 14]. Remission is commonly considered to be DAS28 < 2.6 [13]. A change in DAS28 score of 1.2 is considered to be the minimal clinically important difference [15]. The separate sub-items of DAS28 will also be analyzed.

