### Statistical analysis

All statistical analyses will be conducted by a statistician blinded to group allocation with the SAS package. The level of significance will be set at 5% in a two-tailed test. Multiple imputation methods will be used to replace missing values.

The analysis set will consist of a full analysis set, a per protocol (PP) set, and a safety set. The full analysis set will include all randomized participants who have received any study treatment and had at least one assessment after treatment. The PP set will include only participants who have completed the treatment according to the protocol. The minimum compliance rate of participants receiving the investigational drugs for the PP set is 80%. The safety set will include any participants who were randomly assigned and have received at least one investigational drug. The main analysis will use the full analysis set. It will be compared to the PP analysis as a sensitivity analysis. An interim analysis will not be performed.

For the descriptive analysis, Student’s *t*-test or a Wilcoxon rank sum test for continuous data and a chi-squared test or Fisher’s exact test for categorical data will be performed.

For a confirmatory analysis, an analysis of covariance will be conducted to compare the mean differences in DAS28 scores between the two groups by substituting each group and the 12-item BSQ score for fixed factors, points acquired at baseline for covariates, and points assessed at week 12 for dependent variables. The secondary outcomes will be analyzed following the same methodology used for the primary outcome. A repeated measures analysis of variance will be used to identify any trend changes.

A safety assessment will be performed for all AEs occurring during the study period. The incidence of AEs, AEs leading to withdrawal, and serious AEs will be summarized by group and analyzed using Fisher’s exact test or a chi-squared test.

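### Steroid injections are banned on study because they can affect the primary outcome, but the entry criterion leaves recent intramuscular, intravenous and non-evaluated-joint injections uncontrolled

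*Protocol article*

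**What the plan says.** Two rules deal with steroid injections.

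- **On study** (Prohibited concomitant treatments): "Prohibited drugs include agents that can affect RA and the primary outcome, such as (1) DMARDs except methotrexate, (2) steroid injections". No site or route is specified.
- **Before entry** (Exclusion criteria): a steroid injection within 4 weeks of screening excludes a patient only if it went into the glenoid cavity of the evaluation joint.

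The next exclusion criterion opens with oral steroids above 10 mg per day and goes on to new starts within 4 weeks and dose changes within 2 weeks. Its counterpart under Permitted concomitant treatments is explicitly about oral use: "Oral steroids (less than 10 mg per day) and NSAIDs started for at least 4 weeks with the dose maintained for at least 2 weeks".

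Eligible patients are "requested to visit for randomization within 2 weeks of the screening visit" (Study plan).

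The endpoint is described as follows: "Changes in DAS28 based on erythrocyte sedimentation rate (ESR) scores will be used as the primary outcome measurement". The analysis of covariance takes "points acquired at baseline for covariates, and points assessed at week 12 for dependent variables" (Statistical analysis).

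**The concern.** The protocol accepts that steroid injections can alter the primary outcome, and it sets a 4-week look-back for one kind of injection. The wording of that look-back does not cover the whole class that the on-study rule names.

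The systemic routes matter most. An intramuscular or intravenous dose can lower joint counts, ESR and the patient's global assessment together, and these are the components of DAS28-ESR. If it is given shortly before screening, baseline is measured under an effect that may fade over the 12 weeks. Baseline is both the reference for change and the ANCOVA covariate, so such a patient tends to look worse at week 12 in either arm.

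Other treatments active in RA do have an entry control. Methotrexate must be stable for 8 weeks, oral steroids and NSAIDs have start and dose-change windows, and other DMARDs and biologics are excluded. Injections are the class whose control is only partial.

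**Working it through.** **1. Who is excluded under each reading of the entry criterion**

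| Steroid injection shortly before screening | Literal reading (shoulder socket) | Read as joint cavity | On-study rule |
|---|---|---|---|
| Shoulder, evaluated | excluded | excluded | prohibited |
| Other evaluated joint (e.g. knee, wrist) | not excluded | excluded | prohibited |
| Joint that is not evaluated | not excluded | not excluded | prohibited |
| Intramuscular or intravenous | not excluded | not excluded | prohibited |

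The last two rows stay open under either reading.

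**2. Whether another rule closes the gap**

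- The oral-steroid criterion and its permitted-treatment counterpart concern oral dosing.
- The investigator may exclude patients judged unsuitable, but this is discretionary and does not mention injections.
- The interval from screening to randomization is at most 2 weeks, with no minimum, so it does not act as a washout.
- The activity floors are DAS28 of at least 3.2 and "Patients with at least three swollen joints and three tender joints". They remove strongly suppressed patients only. Someone suppressed from 5.0 to 4.0 still qualifies on DAS28.

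**3. Planned size**

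The Sample size section starts from 12 per group and allows 20% dropout: 12 / (1 − 0.20) = 15 per group, 30 in total. This reproduces, and the fix does not change it.

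**4. Size of the effect**

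The documents give neither the frequency of recent injections nor their effect on DAS28. All inputs here are assumptions: k more injected patients in one arm than in the other, baseline lowered by d = 0.6 to 1.2 points, effect gone by week 12, and ANCOVA baseline slope b = 0.5.

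- Shift in the arm difference in change = k × d / 15.
  - k = 1, d = 0.6: 0.04.
  - k = 3, d = 0.6: 0.12.
  - k = 3, d = 1.2: 0.24.
- Shift in the ANCOVA estimate = b × k × d / 15. For k = 3 this is 0.5 × 0.12 = 0.06 to 0.5 × 0.24 = 0.12.
- Chance that all 3 of 3 injected patients fall in one arm (15 and 15) = 2 × C(15,3) / C(30,3) = 2 × 455 / 4060 = 0.224.
- For injection prevalence p = 5% to 20%:
  - SD of the chance difference in mean baseline = d × √(2p(1 − p)/15). It is 0.05 at p = 5%, d = 0.6, and 0.18 at p = 20%, d = 1.2.
  - Mean upward drift in both arms = p × d, from 0.05 × 0.6 = 0.03 to 0.20 × 1.2 = 0.24.
- Simulated ANCOVA (15 per arm, SD 1, baseline to week 12 correlation 0.5, d = 1.2): the SD of the treatment estimate is 0.320 with no injected patients, 0.329 with 3 and 0.333 with 6, an increase of about 3 to 4%.

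**5. Set against the plan's own yardstick**

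The article states: "A change in DAS28 score of 1.2 is considered to be the minimal clinically important difference". The k = 3 ANCOVA shift is 0.06/1.2 = 5% to 0.12/1.2 = 10% of that, or about 0.2 to 0.4 of a standard error of 0.32.

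**The case against.** The strongest objection is to the shoulder-only reading, which a reader might take from the literal words. The criterion goes on to refer to the evaluation joint, and the evaluated joints are the 28 joints of the DAS28, most of which have no glenoid cavity in the shoulder sense. A mistranslation of joint cavity is much the likelier explanation. On that reading recent knee, wrist or finger injections are already excluded. This stands, and the point does not depend on the literal reading.

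A second tempting inference is that the gap biases the comparison between arms. The document does not support that. Allocation is random and double-blind, and baseline is a covariate, so injected patients are equally likely to fall in either arm and the expected between-arm bias is zero. Nor does anything in the article show that such patients would have little chance of an ACR or EULAR response.

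Three further arguments stand in part.

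- **A broad on-study ban and a narrower look-back are not a formal contradiction.** That is true. But the 4-week window shows that the sponsor wanted to control recent injections, and the route most able to move DAS28 is outside it.
- **The clause on changed steroid dose within 2 weeks could be stretched to a systemic injection.** It could, but it sits in an oral-steroid criterion and its counterpart says oral.
- **The full protocol may define routes.** It may, but the criterion printed here is specific and limits itself to one site.

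Injection into a non-evaluated joint does not act directly on the 28-joint counts, so that part of the gap matters less than the systemic routes.

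**Conclusion.** The point holds as an incomplete entry criterion of modest consequence. As written, a patient given intramuscular or intravenous steroid, or an injection into a non-evaluated joint, days before screening can be randomized with a temporarily low baseline DAS28-ESR. The result is a little more noise, possible chance imbalance with 15 per arm, and upward drift in both arms.

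The size rests wholly on assumed inputs. The all-in-one-arm case for three patients has probability 0.224 given that exactly three are affected, and is well below one standard error. The drift common to both arms bears on the pilot's use for planning, because the trial is meant to inform the sample size of a definitive study and to test its eligibility criteria. It does not threaten the pilot's validity.

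**What to change.** Reword the exclusion criterion to cover any intra-articular (any joint), intramuscular or intravenous steroid injection within 4 weeks of screening. This keeps the window already in the protocol, replaces the anatomical slip, and adds the missing routes. It need not extend to local injections outside joints.

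The cost is one reworded criterion in an amendment and a few candidates deferred or screened out, in a population already restricted to methotrexate without other DMARDs. The sample size and the analysis do not change.

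Trial status expects recruitment to be complete by July 2018. If enrolment has closed, carry the corrected criterion into the definitive trial.
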